#### **9.2.2 Serious adverse events (SAEs)**

A serious adverse event is any untoward medical occurrence or effect that

- results in death;
- is life threatening (at the time of the event);
- requires hospitalization or prolongation of existing inpatients' hospitalization;
- results in persistent or significant disability or incapacity;
- is a congenital anomaly or birth defect; or
- any other important medical event that did not result in any of the outcomes listed above due to medical or surgical intervention but could have been based upon appropriate judgement by the investigator.

An elective hospital admission will not be considered as a serious adverse event.

All SAEs will be discussed with participating surgeons/ urologists.

All SAEs will be reported through the web portal *ToetsingOnline* to the accredited METC that approved the protocol, within 15 days after the sponsor has first knowledge of the serious adverse reactions.

SAEs that result in death or are life threatening should be reported expedited. The expedited reporting will occur not later than 7 days after the responsible investigator has first knowledge of the adverse reaction. This is for a preliminary report with another 8 days for completion of the report.

Complications which are directly related to the surgical procedure will not be reported, but will be registered (primary outcome), including:

- wound infection
- rebleeding
- abscess formation
- fascial dehiscence

#### **9.2.3 Suspected unexpected serious adverse reactions (SUSARs)**

Not applicable.

### **9.3 Annual safety report**

Not applicable

### **9.4 Follow-up of adverse events**

All AEs will be followed until they have abated, or until a stable situation has been reached. Depending on the event, follow up may require additional tests or medical procedures as indicated, and/or referral to the general physician or a medical specialist.

SAEs need to be reported until the end of the study, as defined in the protocol.

### **9.5 Data Safety Monitoring Board (DSMB) / Safety Committee**

Patients included in the intervention group will be screened for physical fitness prior to the start of prehabilitation. Patients screened at risk will be referred to a cardiologist or pulmonologist to undergo additional tests (e.g. ECG, spirometry, cardiopulmonary exercise test) to assess whether undergoing high intensity training (HIIT) during prehabilitation is safe. Moreover, the content of the prehabilitation program is adapted to each individual participant. Physical measurements and high intensity exercise will be performed under supervision of a 1st line physiotherapist or dietician. If necessary, the program can be adapted throughout the trial over again. Participating in this trial does not alter or delay the treatment in any way. Therefore, the risk of participating

in this trial is negligible and therefore the use of a Data Safety Monitoring Board (DSMB) is not necessary.

## 10. STATISTICAL ANALYSIS

For this section we consulted [name], department of Epidemiology, Radboudumc.

The principle investigator ([name]) has final responsibility with regard to the data. Castor EDC will be used to minimize errors and to ensure traceability.

Data will be analyzed according to a detailed statistical analysis plan, which will be available before the final data freeze to allow for corrections based on data checks and database cleaning.

### 10.1 Primary study parameter(s)

Data will be analyzed on an intention-to-treat basis. In addition, a per-protocol analysis will be performed.

The primary outcome is postoperative complications. Data will be collected as a continuous variable and calculated through the sum of morbidity and mortality presented on the Clavien-Dindo classification(42). CCI score will be calculated at the 30 day follow up.

This study aims to show a 20% relative reduction in the percentage of Clavien-Dindo score II or higher. To test this, a log-binomial model (generalized linear model with log link and binomial error distribution) will be fitted with clusters (categorical variable), treatment arm, and time (as linear continuous) as fixed effects. Fixed effects for clusters are chosen as the aim is primarily to establish the effect for the Radboudumc. As secondary analyses, both Clavien-Dindo classification and CCI score will be analyzed as semi-continuous scores using generalized linear models with log-link, normal distribution for the errors, and the same fixed effects. Other parametrizations may be investigated if these improve the model fit (e.g, random effects for clusters, other error distributions for instance to account for zero-inflation).

### 10.2 Secondary study parameter(s)

All secondary data will be described by means plus SD per time point. Generalized linear models as described for the primary parameters will be used. This will be done by using the appropriate link-function (i.e. linear, log, logistic) and error-distribution (i.e, normal, binary). If data are continuous and non-normally distributed, data will be described by means plus IQR per time point. Categorical parameters will be described as number plus percentage per time point. Statistical methods will include t-test and Mann-Whitney U test for continuous normally respectively non-normally distributed parameters at a single time-point post-operatively. Categorical outcomes will be analyzed by using Chi-square tests or (logistic, ordinal or nominal, depending on the definition of the parameter) regression analysis for single time points.

For this section we consulted [name], department of Health Evidence, Radboudumc

The cost-effectiveness analysis will be performed from a healthcare perspective. The aim of the economic evaluation is to measure, value and analyze healthcare costs at a patient's level in patients undergoing usual preoperative care and patients undergoing a multimodal prehabilitation program. The time horizon of the economic evaluation is 12 months after surgery. The analysis will be performed along-side the stepped wedge trial with the primary outcome of the study (postoperative complications).

Standard cost prices for postoperative complications and both prehabilitation programs (PREHAB SHORT and PREHAB LONG) will be determined based on the 'Kostenhandleiding'(63). Data on costs due to postoperative complications will be collected throughout the study in Castor EDC. A multi-level generalized linear model (with gamma distribution and log-link function if data are non-normally distributed) will be used for the cost analysis with chosen fixed effects for time and random effects for clusters.

Additionally, a cost-utility analysis will be performed with quality-adjusted life-years (QALYs) based on the EQ-5D-5L at 6 months after surgery, following the Dutch guidelines of economic evaluation in healthcare(64).

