#### 2. Preoperative period

##### A. Without intervention (standard preoperative care)

Patients will undergo standard preoperative care according to Dutch guidelines(39). To collect data, two additional appointments will be combined with regular, preoperative outpatient clinic visits. Patients will undergo measurements regarding physical fitness, nutritional status and health status as shown in Appendix I.

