#### 8.1.2 Secondary study parameters/endpoints

The following secondary outcomes are studied in this cohort study:

| Outcome                                 | Tool used                                                                                     | Expressed in                | Measured at                                         |
|-----------------------------------------|-----------------------------------------------------------------------------------------------|-----------------------------|-----------------------------------------------------|
| Length of hospital stay (LOS)           | -                                                                                             | In days                     | Surgery +4 weeks                                    |
| Change in physical fitness and activity | Estimated VO 2 peak (submaximal Astrand-Rhyming test)                              | Milliliters/kilogram/minute | Baseline
Surgery -1 week                         |
|                                         | Indirect 1 repetition measures (1RM)                                                          | Weight in kilograms         | Baseline
Surgery -1 week                         |
|                                         | Physical activity (Short Questionnaire to Assess Health-enhancing physical activity (SQUASH)) | Minutes per week            | Baseline
Surgery +6 months
Surgery +12 months |
| Change in nutritional status            | Body weight                                                                                   | In kilograms                | Baseline
Surgery -1 week                         |
|                                         | Fat-free mass (Bio Impedance Analysis (BIA))                                                  | Weight in kilograms         | Baseline
Surgery -1 week                         |
|                                         | PG-SGA                                                                                        | Score (A, B or C)           | Baseline
Surgery -1 week                         |

|                                                                               |                                                                                                     |                                      |                                                                        |

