- The submaximal Astrand-Rhyming test will be used to estimate a patient's cardiorespiratory fitness. It is a simple, 6-minute, non-maximal cycle ergometer test(47) and therefore safer and better tolerated than maximal testing procedures, irrespective of the accuracy of the VO2 peak prediction(48).

- The indirect 1 repetition measures (1RM) are used to dose the training and will be determined based on chest press and leg press to assess the impact of the intervention throughout the perioperative period(49). The 1RM is calculated by the Brzycki formula:  $1RM = W \cdot 36 / (37 - r)$  (w=weight, r=repetitions)(50).
- The Patient-Generated Subjective Global Assessment (PG-SGA) screening tool will be used to identify malnutrition. This is an internationally validated instrument and preferred screening method to identify malnutrition in oncologic patients(20, 51-54). The energy requirements of the patient. Is calculated by the WHO formula.. Håkonsen et al recommended the PG-SGA as a nutritional assessment tool in colorectal cancer patients in combination with other parameters(55). The PG-SGA consists of two parts: 1) the first part is the Patient Generated Subjective Global Assessment Short Form (PG-SGA SF) which includes a brief questionnaire addressing current weight, weight history, acute weight changes, changes in food intake over the past month, occurrence of nutrition impact symptoms experienced over the previous 2 weeks and changes in physical activities and functions over the previous month. The PG-SGA SF will be completed by patients themselves and generates a score for nutrition risk. The PG-SGA SF is a widely validated malnutrition screening tool in cancer patients(56). 2) the second part will be completed by the dietician and includes a physical examination, where fat and muscle stores an fluid status are assessed, and assessment of the disease/ condition and metabolic demand. The global PG-SGA generates a subjective category rating for nutritional status: well-nourished (PG-SGA A), suspected malnutrition or moderate malnutrition (PG-SGA B), or severe malnutrition (PG-SGA C). It also provides a numeric score used for triaging nutritional intervention, i.e. to indicate the need for protein andcalorie (en)rich(ed) diet. PG-SGA will be measured at baseline and 1 week before surgery.

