## 14. APPENDICES

### Appendix I: Overview of measurements

| OK -4w/OK -8w                                                                                                 | OK -1w                                                                              | OK | OK +1m                      | OK +6m                                                      | OK +12m                                            |
|---------------------------------------------------------------------------------------------------------------|-------------------------------------------------------------------------------------|----|-----------------------------|-------------------------------------------------------------|----------------------------------------------------|
| Screening
(in intervention group)                                                                   | Health behavior questionnaire                                                |    | Postoperative complications | Physical activity
- SQUASH questionnaire          | Physical activity
- SQUASH questionnaire |
| Physical fitness and activity
- submaximal Astrand test
- indirect 1RM
- SQUASH questionnaire | Physical fitness and activity
- submaximal Astrand test
- indirect 1RM |    | Length of stay              | Mental health
- SF-36 questionnaire
- EQ-5D-5L | Mental health
- SF-36 questionnaire      |
| Nutritional status
- length, body weight
- fat-free mass (BIA)
- 3-day food diary             | Nutritional status
- body weight
- fat-free mass (BIA)
- PG-SGA     |    |                             |                                                             |                                                    |
| Mental health
- SF-36 questionnaire                                                                 | Mental health
- SF-36 questionnaire                                       |    |                             |                                                             |                                                    |

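### Section 10.2 does not define the response for the 'change' outcomes and uses no baseline covariate, and Appendix I conflicts with Table 5 and section 8.4 on baseline PG-SGA

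*Protocol*

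**What the plan says.** Protocol section 10.2 carries the primary model over to the secondary outcomes: "Generalized linear models as described for the primary parameters will be used". It then adapts the link function and error distribution to the outcome type. The terms of that model are in 10.1, where it "will be fitted with clusters (categorical variable), treatment arm, and time (as linear continuous) as fixed effects". Section 10.2 adds: "Statistical methods will include t-test and Mann-Whitney U test for continuous normally respectively non-normally distributed parameters at a single time-point post-operatively". Categorical outcomes get chi-square tests or logistic, ordinal or nominal regression at single time points.

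Table 5 (section 8.1.2) groups most patient-level outcomes under labels such as "Change in physical fitness and activity". It schedules a baseline measurement for estimated VO2 peak, 1RM, SQUASH, body weight, fat-free mass, PG-SGA and SF-36. EQ-5D-5L is scheduled at 6 months only.

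On PG-SGA, section 8.4 states without restriction by condition: "PG-SGA will be measured at baseline and 1 week before surgery". Table 5 agrees. Section 5.1, part 2.A, says of control patients: "Patients will undergo measurements regarding physical fitness, nutritional status and health status as shown in Appendix I". In Appendix I the baseline nutritional list is length, body weight and then "fat-free mass (BIA) - 3-day food diary". PG-SGA appears only in the column for one week before surgery.

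**The concern.** Three things do not fit together.

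- **The response is undefined.** Table 5 speaks of change, while 10.2 speaks of models and single-time-point tests. An analyst could model the follow-up value or the difference from baseline and claim support for either.
- **Baseline has no place as a covariate.** Baseline is measured in both conditions and is usually a strong predictor of the later value. The covariate set in 10.1 was written for postoperative complications, which have no baseline value. It was carried over to outcomes that do have one.
- **The PG-SGA schedule contradicts itself.** A change in PG-SGA needs a baseline rating in both conditions, and the schedule that control patients follow does not list one.

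At stake are the precision of the secondary comparisons and their exposure to baseline differences. Both matter more here than in an individually randomised trial. Under section 8.2 assignment follows calendar time and cluster. In the section 3 diagram the first cluster to switch has no prospective control month and the second has one. The fitness tests and questionnaires presumably exist only for prospective patients, so information on these outcomes is thinner than for the primary.

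**Working it through.** The protocol gives no precision or power figure for secondary outcomes, so there is nothing of its own to reproduce. The 83% power in section 4.4 concerns the primary outcome and is not touched.

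**1. Precision.** Assume a continuous outcome with equal within-cluster variance s² at baseline and follow-up, within-cluster correlation r, and an identity link. The residual variances are:

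- follow-up value alone: s²
- change score: 2(1 − r)s²
- follow-up value adjusted for baseline: (1 − r²)s²

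Adjustment therefore saves r² against the follow-up value. Against the change score it saves 1 − (1 − r²)/[2(1 − r)] = 1 − (1 + r)/2 = (1 − r)/2. The documents give no r, so a range is shown, with variances in units of s²:

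| r (assumed) | Follow-up | Change | Adjusted | Saving vs follow-up | Saving vs change |
|---|---|---|---|---|---|
| 0.4 | 1.00 | 1.20 | 0.84 | 16% | 30% |
| 0.5 | 1.00 | 1.00 | 0.75 | 25% | 25% |
| 0.6 | 1.00 | 0.80 | 0.64 | 36% | 20% |
| 0.7 | 1.00 | 0.60 | 0.51 | 49% | 15% |
| 0.8 | 1.00 | 0.40 | 0.36 | 64% | 10% |

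**2. In this design.** The Table 2 volumes sum to 1404 a year (section 4.4 states 1414, a difference of 0.7%). Section 4.3 expects 60–80% accrual. At 70%, the 24 prospective months give 2 × 1404 × 0.7 ≈ 1,966 patients. With 20 cluster effects, linear time and random switching orders, the standard errors of the treatment effect in SD units are:

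| r (assumed) | Follow-up | Change | Adjusted |
|---|---|---|---|
| 0.5 | 0.079 | 0.079 | 0.068 |
| 0.7 | 0.079 | 0.061 | 0.056 |
| 0.8 | 0.079 | 0.050 | 0.047 |

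**3. Baseline imbalance.** Let the intervention patients differ by d SD at baseline, with follow-up depending on the measured baseline with slope r. The error is r·d for the follow-up value and −(1 − r)·d for the change score. With an illustrative d = 0.10 and r from 0.4 to 0.8, that is +0.04 to +0.08 SD and −0.06 to −0.02 SD. Simulation of this design at r = 0.3, 0.5, 0.7 and 0.8 gave errors of the expected size and sign. The baseline-adjusted estimate was within 0.01 SD of the truth each time.

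**4. Response.** In a linear model that includes baseline, the treatment estimate is the same whether the response is the follow-up value or the change. The covariate thus also settles the ambiguity.

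**5. PG-SGA.**

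| Place | Baseline | One week before surgery |
|---|---|---|
| Table 5 | yes | yes |
| Section 8.4 | yes | yes |
| Appendix I, nutritional status | not listed | yes |

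The only Appendix I baseline entry that could cover it is the screening item, marked for the intervention group. That fits the dietician's PG-SGA screening in section 5.1, part 2.B.3. Control patients have no such route in Appendix I.

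**The case against.** The strongest reply is that section 10 defers detail to a statistical analysis plan, which is not shown, and that baseline covariates for secondary outcomes are commonly fixed there. Section 10.1 also leaves room: "Other parametrizations may be investigated if these improve the model fit". Nothing in 10.2 forbids a baseline term. This stands in part: the plan may already contain the covariate. But the protocol does more than defer. It names a covariate set and applies it to these outcomes, and its examples of flexibility are random effects and error distributions.

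A reader might infer that the baseline values are simply wasted and that adjustment is worth two to five times the patients. That ratio is 1/(1 − r²), or 1.96 at r = 0.7 and 5.26 at r = 0.9, and it holds only against unadjusted follow-up values. Table 5 labels the outcomes as changes, so baseline may already enter by subtraction. The saving is then 15% at r = 0.7 and 5% at r = 0.9.

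A reader might also infer that consent with the condition known has biased these comparisons. Assignment by time and cluster makes imbalance possible, but nothing in the protocol shows or quantifies it. The near-zero error under adjustment depends on the mechanism assumed above. If the groups differ in a stable underlying level, adjustment for a measured baseline need not remove the whole difference.

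Finally, a reader might say that Appendix I drops baseline PG-SGA for controls. The appendix omits it for everyone. It is also an incomplete overview, lacking mHLA-DR and hand grip strength, and two places in the body require the measurement. The loss in controls is an inference about what happens if staff follow the appendix. The contradiction itself is plain text.

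**Conclusion.** The point holds in a limited form. Section 10.2 leaves the response for the change outcomes undefined, and neither reading includes baseline as a covariate. Adding it reduces residual variance by 16–64% against follow-up values or 30–10% against change scores, for r from 0.4 to 0.8. These figures rest on assumed within-cluster correlations, equal variances and a linear model. They do not carry over to the three-category PG-SGA rating, and EQ-5D-5L has no baseline to adjust for. Protection against imbalance is a further benefit of uncertain size.

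The PG-SGA mismatch is a separate contradiction in the measurement schedule. No analysis plan can repair it, because a baseline not taken before surgery cannot be recovered. If Appendix I is followed, controls have no baseline PG-SGA and its change cannot be computed for them.

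Only secondary outcomes are affected. The primary analysis and its power are not.

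**What to change.** - **Section 10.2:** state that each continuous secondary outcome with a baseline measurement is analysed as the follow-up value, with its own baseline as covariate plus cluster, condition and calendar time. This model, not the unadjusted single-time-point tests, should give the comparison between conditions.
- **PG-SGA:** use an ordinal model, a class 10.2 already names, with baseline category as covariate and the same other terms.
- **EQ-5D-5L:** say that it is outside this rule because it has no baseline.
- **Appendix I:** list PG-SGA at baseline for both conditions, so that it agrees with Table 5 and section 8.4.

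The cost is a sentence or two in 10.2 and one line in Appendix I. The only fieldwork is a baseline PG-SGA in control patients, which Table 5 and 8.4 already require. The appendix should be corrected first.

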### 3. STUDY DESIGN

This is a monocenter stepped-wedge cluster randomized trial of patients aged >16 years undergoing elective high impact surgery in Radboudumc, Nijmegen. Patients will be grouped into 20 clusters based on diagnosis; colon cancer, rectal cancer, esophageal cancer, liver metastases from colorectal cancer, pancreato-biliary cancer, peritoneal carcinomatosis from colorectal cancer, abdominal aortic aneurysm (open and endovascular), renal cancer, bladder cancer, supratentorial meningioma, hip arthrosis, osteosarcoma, pulmonary cancer, thoracic aortic aneurysm, head and neck cancer, mouth cancer, breast reconstruction, ovarian cancer or endometriosis. The prehabilitation program intervention will commence in one cluster each month with the order of clusters determined by computer based randomization. The stepped-wedge design allow delivery of the intervention at an organizational level with evaluation of outcome measures at a patients level. Structuring the prehabilitation program intervention through a staged activation in a random order provides important methodological advantages. The design allows to control adoption bias and to adjust for time-based changes in the background level of patient care in statistical analysis. A key strength of stepped-wedge design is that the prehabilitation program can be offered to every patient who is undergoing elective high impact surgery in Radboudumc, Nijmegen.

This stepped-wedge cluster randomized trial will be combined with an observational cohort study performed in Radboudumc on surgery induced danger-associated molecule patterns (DAMPs) and innate immune changes in patients undergoing endovascular aneurysm repair(38). Patients within the care path 'abdominal aortic aneurysm' will undergo additional blood tests, according to protocol, to determine the effect of prehabilitation on the innate immune response (see also 8. METHODS).

| Cluster | Pre
(24 months) |     |     |   | Switching (20 months) |   |   |   |   |   |   |   |   |   |   |   |   |   |   |   |   |   |   |   |   |   | Post
(4 months) |   |   |  |
|---------|--------------------|-----|-----|---|-----------------------|---|---|---|---|---|---|---|---|---|---|---|---|---|---|---|---|---|---|---|---|---|--------------------|---|---|--|
| 1       | 0                  | ... | ... | 0 | 1                     | 1 | 1 | 1 | 1 | 1 | 1 | 1 | 1 | 1 | 1 | 1 | 1 | 1 | 1 | 1 | 1 | 1 | 1 | 1 | 1 | 1 | 1                  | 1 | 1 |  |

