| 15      | 0                  | ... | ... | 0 | 0                     | 0 | 0 | 0 | 0 | 0 | 0 | 0 | 0 | 0 | 0 | 0 | 0 | 0 | 1 | 1 | 1 | 1 | 1 | 1 | 1 | 1 | 1                  | 1 | 1 |  |
| 16      | 0                  | ... | ... | 0 | 0                     | 0 | 0 | 0 | 0 | 0 | 0 | 0 | 0 | 0 | 0 | 0 | 0 | 0 | 0 | 1 | 1 | 1 | 1 | 1 | 1 | 1 | 1                  | 1 | 1 |  |
| 17      | 0                  | ... | ... | 0 | 0                     | 0 | 0 | 0 | 0 | 0 | 0 | 0 | 0 | 0 | 0 | 0 | 0 | 0 | 0 | 0 | 1 | 1 | 1 | 1 | 1 | 1 | 1                  | 1 | 1 |  |
| 18      | 0                  | ... | ... | 0 | 0                     | 0 | 0 | 0 | 0 | 0 | 0 | 0 | 0 | 0 | 0 | 0 | 0 | 0 | 0 | 0 | 0 | 1 | 1 | 1 | 1 | 1 | 1                  | 1 | 1 |  |
| 19      | 0                  | ... | ... | 0 | 0                     | 0 | 0 | 0 | 0 | 0 | 0 | 0 | 0 | 0 | 0 | 0 | 0 | 0 | 0 | 0 | 0 | 0 | 1 | 1 | 1 | 1 | 1                  | 1 | 1 |  |
| 20      | 0                  | ... | ... | 0 | 0                     | 0 | 0 | 0 | 0 | 0 | 0 | 0 | 0 | 0 | 0 | 0 | 0 | 0 | 0 | 0 | 0 | 0 | 0 | 0 | 1 | 1 | 1                  | 1 | 1 |  |

Retrospectively, 24 months of pre-measurements will be collected. The prospective data collection will include 20 months in which every month one cluster switches and 4 months of post-measurements. In the above a '0' indicates the control condition and a '1' the intervention condition.

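### Section 10.2 names both a cluster- and time-adjusted model and unadjusted two-sample tests for single-time-point secondary outcomes, with no priority; the unadjusted tests do not hold 5% in this design

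*Protocol*

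**What the plan says.** Protocol section 10.2 begins with descriptive rules and then states: "Generalized linear models as described for the primary parameters will be used". Section 10.1 defines that model as having "clusters (categorical variable), treatment arm, and time (as linear continuous) as fixed effects". Section 10.2 lets the link and error distribution vary with the outcome.

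The same paragraph goes on: "Statistical methods will include t-test and Mann-Whitney U test for continuous normally respectively non-normally distributed parameters at a single time-point post-operatively". For categorical data it says: "Categorical outcomes will be analyzed by using Chi-square tests or", followed by logistic, ordinal or nominal regression, for single time points. No cluster or calendar-time term is mentioned for any of these. The paragraph does not rank the two approaches or confine the simple tests to description.

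Later in section 10.2, costs receive a separate multi-level generalized linear model with fixed effects for time and random effects for clusters.

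Section 3 gives as a reason for the design that it makes it possible to "adjust for time-based changes in the background level of patient care in statistical analysis".

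**The concern.** In a parallel-group trial with individual randomisation, a two-sample test at one time point would be unremarkable. Here the randomised unit is the diagnosis, and treatment is set by diagnosis and calendar month together. Diagnoses that switch early supply mostly intervention patients and those that switch late supply more controls. Intervention patients also come later in time on average. A t-, Mann-Whitney or chi-square test therefore mixes the effect of prehabilitation with case mix and secular change, and its standard error ignores both.

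The outcomes most directly exposed are length of stay and EQ-5D-5L, which is measured only at 6 months after surgery and so has no baseline. SF-36 or SQUASH is exposed if compared at a single post-operative visit. PG-SGA, the one secondary outcome in Table 5 expressed in categories, falls under the chi-square sentence.

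Two analyses that can disagree are both authorised for the same outcome. A length-of-stay or quality-of-life conclusion could then follow from the switch order, or from which permitted test is reported.

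**Working it through.** The protocol states no error rate for the secondary analyses, so there is no figure of its own to reproduce. Its 83% power belongs to the primary log-binomial analysis and does not bear on this point.

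**Inputs**
- 20 clusters, one switching per month over 20 months, then 4 further months (section 3). "Retrospectively, 24 months of pre-measurements will be collected"; all of that period is control.
- Table 2 volumes of 30 to 150 procedures a year per cluster. The rows add to 1404 a year, so 2808 over 24 months.
- Accrual of 60-80% (section 4.3); 70% is used below.
- Assumed: two-sided 5% level, ICC between diagnoses from 0 to 0.20, no treatment effect. The protocol does not say which secondary outcomes are collected retrospectively, so both cases are shown.

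**Imbalance built into the design.** The cluster that switches first gives 24 intervention months and no prospective control months. The last gives 5 and 19. Intervention cluster-months are 24 + 23 + ... + 5 = 290 and prospective control months are 480 − 290 = 190. With the pre-period, control months are 190 + 480 = 670.

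**Approximation by hand, equal cluster sizes.** Let k be a cluster's intervention months. Its weight in the intervention mean minus its weight in the control mean is

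d = (k − 14.5)(1/290 + 1/C), with C = 190 or 670.

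Since Σ(k − 14.5)² = 665, S = Σd² = 665(1/290 + 1/C)². This gives 0.0505 (prospective only) or 0.0162 (with pre-months).

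With total variance 1 and ICC ρ, the true variance of the unadjusted difference is (1 − ρ)v + ρS. The simple test assumes about v = 1/n₁ + 1/n₀. At 70% accrual n₁ = 0.7 × 2808 × 290/480 = 1188, and n₀ = 778 or 2744, so v = 0.00213 or 0.00121.

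Example, ρ = 0.05, prospective only: (0.95 × 0.00213 + 0.05 × 0.0505)/0.00213 = 2.14. The effective critical value is 1.96/√2.14 = 1.34, which gives a false-positive rate of 18%. With pre-months the ratio is 1.62, the critical value 1.54 and the rate 12%.

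**Simulation with Table 2 sizes and random switch order** (no effect, no trend, 70% accrual; t-test / Mann-Whitney):

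| ICC (assumed) | Prospective only | With 24 pre-months | By hand (prospective; with pre) |
|---|---|---|---|
| 0 | 5.0% / 4.6% | 4.6% / 4.0% | 5%; 5% |
| 0.01 | 9.3% / 9.0% | 7.2% / 5.8% | 8%; 6% |
| 0.02 | 11.4% / 13.8% | 9.8% / 9.2% | 10%; 8% |
| 0.05 | 23.1% / 21.0% | 13.8% / 16.0% | 18%; 12% |
| 0.10 | 29.0% / 26.4% | 22.4% / 20.8% | 28%; 19% |
| 0.20 | 47.2% / 46.8% | 32.4% / 33.0% | 41%; 29% |

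The hand values mostly run a little lower because unequal cluster sizes increase S.

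**Calendar trend.** A drift of 0.1 SD over the analysed period raises the rate to 10-27% even at ICC 0, and gives 40-44% at ICC 0.20. Without a trend the error can go either way with the switch order. With a trend it has a direction, because intervention patients come later.

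**Binary illustration.** Table 2 rates have a weighted mean of 24.4% and a between-diagnosis share of variance of about 0.09. A chi-square test on an outcome that varied this much would reject in 37% (100% accrual) or 30% (70%) of null trials on prospective data, and in 27% or 21% with the pre-months.

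**With the adjusted model.** Cluster and linear time as fixed effects bring the rate back to 5.5% (no trend) and 4.5% (10% decline) for the log-binomial model, 1500 runs each. For continuous outcomes it is 3-7% (300-500 runs each, so noise of about 2-3 points).

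**The case against.** The best defence is that the right analysis is already in the paragraph. The adjusted model is named first, chi-square is offered as an alternative to regression, and section 10 defers detail to a statistical analysis plan that may settle which result counts. That stands to this extent: a reader might infer that the secondary outcomes have no adjusted analysis at all, and the text does not support that. The defect is two conflicting methods without priority. It remains a defect because the protocol is not silent here. It names the simple tests as methods to be used.

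The scope is also limited:
- **Costs.** A reader might count these among the affected outcomes. They are not affected, because section 10.2 gives them a model with time and cluster effects.
- **Pre-operative measures.** The t-test and Mann-Whitney sentence covers single post-operative time points. Estimated VO2 peak, 1RM, body weight and fat-free mass are measured at baseline and one week before surgery (Table 5), so that sentence does not reach them.
- **mHLA-DR.** It is measured only in aneurysm patients, so the diagnosis-mix argument applies only in part.
- **Table 2 rates.** These describe the primary outcome, which section 10.1 tests with cluster and time in the model. The chi-square figures illustrate the mechanism and are not an estimate for any listed secondary outcome.

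**Conclusion.** The point holds as a conflict within section 10.2 that matters for inference. For length of stay, EQ-5D-5L at 6 months and other single-time-point comparisons, the protocol authorises tests that ignore the two factors determining treatment in this design, next to a model that includes them.

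The size is conditional. A reader might take error rates of 20-45% as a fixed property of the plan. The documents do not support that, because they give no between-diagnosis variation or time trend for any secondary outcome. Without a trend and at 70% accrual, the range runs from 6-9% (ICC 0.01) and 9-14% (0.02), through 14-23% (0.05) and 21-29% (0.10), to 32-47% (0.20). The lower end generally comes from including the pre-months and the upper end from prospective data only.

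That the adjusted model restores about 5% was checked with stable differences between diagnoses and with no trend or a steady one. The primary analysis is not affected.

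**What to change.** In section 10.2, delete the t-test, Mann-Whitney and chi-square tests as inferential methods, or state that they are descriptive only. State that inference for secondary outcomes rests solely on the generalized linear model already named, with cluster, treatment arm and time, and with link and error distribution suited to the outcome. Any logistic, ordinal or nominal regression kept for categorical outcomes should carry the same cluster and time terms. Leave the separate multi-level cost model as written.

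This is an edit of two sentences. It needs no new data, no extra patients and no change to any visit, and it should be made before the outcome data are examined by arm.
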